**Figure 2 F2:**
[figure not shown]
Study flow chart.

### Study protocol

#### Pre-procedural evaluation

After enrollment, patients will undergo the following baseline procedures: physical examination and medical interview; cardiac echocardiogram assessing systolic and diastolic function, as well as valvular function; endothelial function using the EndoPat™ system, a non-invasive method for assessing endothelial function; carotid artery ultrasound and doppler including Intima Media Thickness calculations; and blood and urine analysis as described below.

All participating patients will receive a standard pre-procedural hydration treatment plan consisting of an infusion of isotonic saline at a rate of 0.5 to 1 mL/kg per hour, starting 12 h prior to the procedure and continuing for 12 h after contrast administration. In addition, 1,200 mg of N-acetyl-cysteine will be administered orally twice daily the day before and the day of the procedure.

Each patient will be randomized to one of the following treatment strategies:

**Group 1** - Sham-controlled Group (Figure 3A). The patients will be connected to the RenalGuard System that will not be activated (passive mode).

**Figure 3 F3:**
[figure not shown]
Treatment algorithms of the sham-controlled/passive RenalGuard group (group A) and the active RenalGuard group (group B).

Before the procedure: A standard 18 to 22 gauge catheter will be inserted into a peripheral vein of the arm and a standard Foley catheter will be placed in the bladder for urine collection (as performed routinely for all TAVI procedures). The intravenous (IV) line and the urinary catheter will be connected to the RenalGuard System. The RenalGuard System will be set to 0% match; that is, the urine rate and volume will be measured, but it will not deliver matched IV normal saline. The system will be computed to deliver continues IV normal saline at a rate of 100 cc/h (100 cc/h is the routine average fluid infusion rate in TAVI procedure) during the procedure and up to 6 h after the procedure. Neither a routine IV bolus of saline nor a routine IV furosemide will be given before the procedure.

During the procedure: The urine and infusion volumes will be measured by the RenalGuard system throughout the catheterization procedure and for 6 h after the last contrast dose. Additional IV fluids can be added as needed according to the clinical decision of the anesthesiologist or the attending physician.

We will analyze the quantity and quality of urine during the duration of the procedure.

**Group 2** - Active Group (Figure 3B). Treatment as group 1 and in addition, the RenalGuard system will be activated (active mode).

Before the procedure: A standard 18 to 22 gauge catheter will be inserted into a peripheral vein of the arm and a standard Foley catheter will be placed in the bladder for urine collection (as performed routinely for all TAVI procedures). The IV line and the urinary catheter will be connected to the RenalGuard System. The RenalGuard System will be set to 100% match; that is, the urine rate and volume will be measured and the system will deliver volume of IV normal saline that is matched to the volume of urine produced by the patient. An initial IV bolus (250 ml) of normal saline over 30 min will be administered approximately 90 min before the procedure; in patients with heart failure, the volume of the bolus can be reduced to 150 ml. Furosemide will then be administered as a single intravenous bolus of 0.25 to 0.5 mg/kg at the physician’s discretion. When a urine output rate >300 ml/h will be achieved, the patients will be sent to the catheterization laboratory.

During the procedure: Additional doses of furosemide (up to a maximal cumulative dose of 2.0 mg/kg) will be given in cases where the urine output is below 300 ml/h during treatment. Matched hydration will continue throughout the catheterization procedure and for 6 h after the last contrast dose. Additional IV fluids can be added as needed according to the clinical decision of the anesthesiologist or the attending physician. We will analyze the quantity and quality of urine during the duration of the procedure.

### Blood and urinary samples

Blood samples will be taken at baseline (on admission); before the procedure; and at 6, 12, 24, 48, and 72 h post-procedure. An 18-gauge cannula will be placed in an antecubital vein for blood sampling. Blood sample analyses will be performed using reagents, calibrators and control materials from Bayer Diagnostics (Berkshire, England) on the ADVIA 1650. At baseline each Patient will provide 40 cc of blood for the following blood tests: full chemistry including lipid levels, thyroid function, BNP, NT-BNP, HbA1c, uric acid, and glucose levels; complete blood count; inflammatory biomarker (hs-CRP, fibrinogen, IL-6, IL-1, MMP, Lp-PLA2, procalcitonin, IL-10, IL-35, TNFa, AchE, and cholinergic status); renal function markers including creatinine, NGAL (neutrophil gelatinase-associated lipocalin), FGF23, and Cystatin-C; and endothelial function markers including I-CAM, V-CAM, superoxide dismutase ADMA, and oxidized LDL. Serum and plasma samples will be frozen for future tests.

Urine samples will be taken at baseline (before the procedure), and after 24 h.

Samples will be taken for basic urinalysis, creatinine, albumin, microalbumin, and electrolytes.

### Study objectives

Reduce-AKI is a prospective, randomized, double-blind, sham-controlled clinical trial of the safety and effectiveness of the RenalGuard system in patients with severe aortic stenosis and eGFR <60 ml/min/1.73 m2 undergoing elective TAVI.

### Primary endpoint

The primary endpoint is reduction of acute kidney injury (stage 1 or above) at 48 to 72 h. Serum creatinine level will be measured prior to TAVI and at 48 to 72 h post-procedure. AKI will be defined as stage 1, 2 or 3 according to VARC-2 AKI classification [15] (Table 1).

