## Background

Acute kidney injury (AKI) is a frequent complication of coronary angiography, and is associated with unfavorable outcomes including major cardiovascular events, renal replacement therapy, prolonged hospitalization, and early death [1,2]. Recently, two randomized controlled trials have demonstrated that furosemide-induced diuresis with matched isotonic intravenous hydration using the RenalGuard system (PLC Medical Systems, Milford, Massachusetts, USA) [3,4] reduces AKI in high-risk patients undergoing coronary procedures.

Elderly patients undergoing TAVI have a high prevalence of chronic kidney disease (CKD) and therefore are at increased risk to develop AKI (Table 1). In recent reports, AKI has been observed in up to 41% of patients undergoing TAVI [5-11] and was associated with a four times higher post-procedural mortality [11-14]. ‘RenalGuard’ is a Conformité Européenne (CE)-approved system that is being used worldwide. The objective of this randomized sham-controlled study is to assess the beneficial effect of treating TAVI patients with this system in reducing the occurrence of AKI.

**Table 1 T1:** **Definition of acute kidney injury post transcatheter aortic valve implantation (TAVI) according to the VARC-2 classification **[15]**]**

**Stage 1**	Increase in serum creatinine to 150 to 199% of baseline
	**OR**
	Increase of ≥0.3 mg/dl (26.4 mmol/L)
	**OR**
	Urine output <0.5 ml/kg/h for >6 but <12 h
**Stage 2**	Increase in serum creatinine to 200 to 299% of baseline
	**OR**
	Urine output <0.5 ml/kg/h for >2 but <24 h
**Stage 3**	Increase in serum creatinine to ≥300% of baseline
	**OR**
	Increase of serum creatinine of ≥4 mg/dL (354 mmol/L) with an acute increase of at least 0.5 mg/dl (44 mmol/l)
	**OR**
	Urine output <0.3 ml/kg/h for >24 h
	**OR**
	Anuria for >12 h

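### Primary AKI is defined by all of Table 1, including urine-output criteria that the active treatment directly alters; the definition should be limited to serum creatinine

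*Protocol article*

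**What the plan says.** **Endpoint.** The Primary endpoint section of the protocol article gives one measurement: "Serum creatinine level will be measured prior to TAVI and at 48 to 72 h post-procedure". The next sentence sets the definition: "AKI will be defined as stage 1, 2 or 3 according to VARC-2 AKI classification", with a pointer to Table 1.

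**Table 1 (Background).** The criteria within each stage are joined by OR, and each stage has a urine-output criterion. Stage 1 can be met by "Urine output <0.5 ml/kg/h for >6 but <12 h". Stage 2 has the same rate with a longer upper limit. Stage 3 can be met by "Urine output <0.3 ml/kg/h for >24 h" or by anuria for more than 12 h. The article nowhere says that the urine criteria are set aside.

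**Active arm (Study protocol, Group 2).** "When a urine output rate >300 ml/h will be achieved, the patients will be sent to the catheterization laboratory". Further furosemide, up to a cumulative cap, "will be given in cases where the urine output is below 300 ml/h during treatment". The infusion of saline matched to urine volume runs over the whole procedure and ends 6 h after contrast was last given.

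**Sham arm (Study protocol, Group 1).** The device is set to 0% match and infuses saline at 100 cc/h. No routine pre-procedural bolus or furosemide is given. The device records urine and infusion volumes "throughout the catheterization procedure and for 6 h after the last contrast dose".

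**The concern.** Urine output is both a route to the primary event and the quantity that the active treatment is titrated to. Within the treatment period, an active patient at target cannot meet the oliguria criterion, whatever is happening to the kidney. A sham patient can. The only period for which the article describes volume recording is that same period.

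If adjudicators apply the definition as written, urine-only events could therefore accrue mainly in the sham arm. The trial could then report less AKI with the device even if creatinine behaved identically in both arms. A larger sample would not correct this.

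**Working it through.** **1. The plan's own figure.** Inputs from Power analysis: 40% vs 20%, two-sided alpha 0.05, power 80%.

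- n = [1.96·√(2·0.30·0.70) + 0.8416·√(0.40·0.60 + 0.20·0.80)]² / 0.20² = 81.2, so 82 per group.
- With continuity correction: (81.2/4)·[1 + √(1 + 4/(81.2·0.20))]² = 90.9, so 91 per group.

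The stated 92 reproduces to within one patient. The sample-size arithmetic is sound. Of the planned 110 per group, 5% dropout leaves 110 × 0.95 = 104.5, taken as 104.

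**2. Distance between target and threshold.** Body weight is not given, so 60 to 100 kg is assumed.

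| Weight | 0.5 ml/kg/h | 300 ml/h divided by threshold |
|---|---|---|
| 60 kg | 30 ml/h | 10.0 |
| 70 kg | 35 ml/h | 8.6 |
| 80 kg | 40 ml/h | 7.5 |
| 100 kg | 50 ml/h | 6.0 |

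**3. Fit of the windows.** The procedure plus 6 h exceeds the 6 h minimum for Stage 1. It also exceeds the 2 h minimum printed for Stage 2. The Stage 3 durations can run past the end of the recording that the article describes.

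**4. Effect on the primary test.** Let c be the creatinine-AKI rate, equal in both arms (no kidney protection). Let s be the share of the remaining sham patients who qualify on urine alone, with none in the active arm. Sham AKI is then c + s(1 − c), and active AKI is c. The table gives the exact binomial probability that a two-sided chi-square test yields P<0.05 with 104 per arm and c = 30%.

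| s | Sham | Active | Chance of P<0.05 |
|---|---|---|---|
| 0% | 30.0% | 30% | 5.1% |
| 2% | 31.4% | 30% | 5.6% |
| 5% | 33.5% | 30% | 8.5% |
| 10% | 37.0% | 30% | 18.9% |
| 20% | 44.0% | 30% | 56.2% |

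**5. A second parameterisation.** Hold sham AKI at the plan's 40% and let u be the part of it that is urine-only (normal approximation, 104 per arm). If diuresis removes all urine-only cases in the active arm, the chance is 6.0%, 11.5% and 32.6% for u = 2%, 5% and 10%. If it removes only half, it is 5.2%, 6.6% and 11.5%.

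**6. What a creatinine-only endpoint does to power.** This applies if the assumed 40% includes urine-only cases. Same exact test, true 50% reduction, 104 per arm:

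| Sham vs active | Power |
|---|---|
| 40% vs 20% | 89.2% |
| 30% vs 15% | 74.5% |
| 20% vs 10% | 53.3% |

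**The case against.** **Creatinine may be what was meant.** It is the only measurement tied to the endpoint, and nothing says that the device volumes feed AKI adjudication. This is a fair reading, and it is why the point is conditional. It does not remove the problem, because the sentence that sets the definition adopts the whole table.

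**Treatment ends early.** The endpoint is assessed at 48 to 72 h, and forced diuresis stops 6 h after the last contrast dose. Later oliguria can occur in either arm. The 300 ml/h figure is a target under a furosemide cap, not a guarantee. A reader might infer that almost no active patient could ever qualify on urine, or that volume is recorded only in the device window. The article supports neither: it describes recording in that window and is silent on the rest. The zero in the active arm in step 4 is therefore an assumption, and step 5 shows the effect of halving it.

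**The sham arm is hydrated.** It receives 100 cc/h, and all patients are to receive saline at 0.5 to 1 mL/kg/h from 12 h before to 12 h after contrast. If both run together, an assumed 70 kg sham patient receives 35 to 70 plus 100, or 135 to 170 ml/h, against a 35 ml/h threshold. Sustained oliguria on that intake may be a genuine renal signal, and large urine-only shares become less plausible. It would go too far to say that the urine component carries no information about the kidney. The remaining point is that the signal can be masked by treatment in one arm only.

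**VARC-2 is a published classification.** Citing it does not settle whether a component that the treatment directly alters belongs in this comparison.

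**Conclusion.** The point stands in conditional form. The article names creatinine as the endpoint measurement but defines AKI by a table in which urine output alone suffices. If those criteria are applied, the comparison can lean toward the device with no kidney protection.

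The direction follows from the design; the size does not. With 30% creatinine-AKI in both arms, 104 per arm and no urine-only active cases, the false-positive chance is about 6% at a 2% urine-only share among the remaining sham patients, 9% at 5%, 19% at 10% and 56% at 20%. Near a zero share it is negligible. A reader might infer that the trial is certain to be biased, or that the upper figures are expected. The documents do not support this, because they give no urine-only share. The planned sample size is not in error for the rates it assumes.

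**What to change.** In the Primary endpoint section, state that primary AKI is judged on the serum-creatinine criteria of Table 1 only and that the urine-output criteria are not used for it. Report AKI by the full table, including urine output, as a secondary result, and say over what period urine volume is assessed.

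In Power analysis, confirm that the 40% sham rate refers to creatinine-defined AKI. If it includes urine-only cases, restate the power.

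The wording change costs little. Creatinine is already measured before TAVI and at 48 to 72 h, and Trial status reports 41 of the planned 220 patients recruited. The real cost is possible loss of events: for a 50% reduction at 104 per arm, power is about 75% at a 30% sham rate and 53% at 20%, against the planned 80%.

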### Secondary endpoints

The secondary endpoints are to assess whether the RenalGuard system can reduce major adverse clinical events (MACE) defined as a composite of all-cause mortality, myocardial infarction, AKI, 30 day readmission rate, and dialysis. Another secondary endpoint is to assess whether the RenalGuard system can lower 30-day readmission rate and 30-day congestive heart failure exacerbation rate.

Other secondary objectives are to determine whether endothelial function assessment can predict AKI using the EndoPat™ system, to determine whether chronic statins treatment offers any clinical benefit in preventing contrast induced nephropathy, to determine if carotid Doppler analysis can predict AKI occurrence and to determine the predictive value of different biomarkers in assessing the clinical outcome in TAVI patients.

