### Transcatheter aortic valve implantation procedures

All patients will undergo transfemoral aortic valve implantation per standard clinical practice. Briefly, the femoral artery will be accessed with the standard endovascular technique, thereafter the procedure involves advancing a large catheter (18 Fr) through the aortic arch, retrogradely crossing the aortic valve, following by balloon valvuloplasty and stent-valve implantation. During the procedure, the patients will receive analgesics and anxiolytics as per protocol.

Post-procedural pharmacotherapy, sheath removal, and deployment of hemostatic devices will be left to the discretion of the attending cardiologists. Following treatment in the catheterization laboratory, medical treatment throughout hospitalization and follow-up treatment will be left to the discretion of the treating physician managing patient care on the hospital wards. Specific agents added or withdrawn will be made by treating physicians and will not be influenced by the study team.

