### Randomization and blinding

At the time of enrollment, signed informed consent will be obtained as per the Tel Aviv Medical Center institutional ethical board standards. After signing the informed consent, patients will be randomized in a 1:1 fashion using closed envelopes. They will be randomized to the active use of RenalGuard system versus using passive use of the RenalGuard system using normal saline 0.9% infusion (sham-controlled group) (Figure 2). The RenalGuard system will be covered before, during and after the procedure with a bag in order to allow effective blinding. All participants will remain blinded throughout the 6-month study period. The interventional cardiologist conducting the TAVI procedure is also blinded to the study treatment arm. The supervising physician, core labs, the biostatisticians performing the analysis, the members of the Clinical Event Committee (CEC), as well as the members of the Data Safety Monitoring Board (DSMB) are blinded to treatment assignment until study completion and after the database has been unlocked.

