### Statistical analysis

Standard statistical analyses will be used to compare the aforementioned endpoints in both study arms. We will compare the incidence of AKI and any clinical differences between the groups. Between-group comparisons of clinical endpoints, biomarkers, and imaging data will be performed using the Mann-Whitney U, independent Student’s t tests, or chi square test according to the distribution of variables. All values will be expressed as medians and interquartile ranges for non-normally distributed continuous variables and as mean and standard error for normally distributed variables.

The statistical analysis of the primary endpoint will performed and presented following the intent-to-treat (ITT) principle. A second set of analysis will be performed using a per-protocol population which will include all enrolled patients who completed the procedure and had a 6-month follow-up. Reported *P* values will be two-sided, and *P* <0.05 will be considered as statistically significant. All analyses will be performed using SPSS statistical software.

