## Discussion

The Reduce-AKI trial will investigate whether the use of forced diuresis with matched saline infusion using the RenalGuard system will reduce the occurrence of AKI in patients undergoing elective transfemoral TAVI.

AKI following TAVI is an independent predictor of short- and long-term outcome [6,11] In previously published studies, the incidence of AKI in patients undergoing TAVI ranged from 12% to 41% [6,9-11] with dialysis required in 1.5 to 10% [6,16].

The reasons for the increased risk of AKI in patients undergoing TAVI include elder population with multiple comorbidities, peri-procedural bleedings, hemodynamic instability, distal embolization and the use of nephrotoxic drugs.

Hydration is the cornerstone of AKI prevention. It increases the intravascular blood volume, suppresses the renin-angiotensin-aldosterone system, and promotes dilution and rapid evacuation of contrast media [4,9,17].

Furosemide may reduce the nephrotoxic effect of contrast media, first by increasing the urine flow and thus diluting the contrast media, and second by blocking tubular sodium reabsorption in the loop of Henle, thus reducing tubular workload and concomitant oxygen requirement.

The use of furosemide alone is controversial since it reduces the effective circulating volume and prostaglandin mediated vasodilation, and may lead to dehydration as a result of increased urine output [18,19]. However, when combining hydration with furosemide, studies have shown improved outcomes [3,4].

The RenalGuard system combines all the above methods for prevention of AKI and hydration with forced diuresis with furosemide, while preventing dehydration or fluid overload.

Recently, two randomized controlled trials [3,4] have demonstrated that furosemide-induced diuresis with matched isotonic intravenous hydration using the RenalGuard system reduces AKI in high-risk patients undergoing coronary procedures by up to 71%. In the present study, we chose to evaluate the effect of the RenalGuard system on patients with reduced eGFR since they are at the highest risk for AKI [6,7,20]. In most TAVI patients present with an eGFR below 60 ml/min/1.73 m2, the low eGFR is mostly due to their advanced age (above 80 years). The inclusion/exclusion criteria were very lenient in order to simulate ‘real life’ patients. Therefore, we believe that the Reduce-AKI study will demonstrate a reduction of AKI in this high-risk patient population.

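### The statin objective is worded as a preventive effect on contrast nephropathy, but the trial can only estimate an observational association with VARC-2 AKI (minor)

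*Protocol article*

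**What the plan says.** The protocol article, Secondary endpoints, lists four further objectives. Three are about prediction: of AKI by endothelial function, of AKI by carotid Doppler, and of clinical outcome by biomarkers. The fourth is "to determine whether chronic statins treatment offers any clinical benefit in preventing contrast induced nephropathy".

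Randomization and blinding shows what is allocated: "They will be randomized to the active use of RenalGuard system versus using passive use of the RenalGuard system". Statins are not mentioned anywhere else in the article.

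The Primary endpoint section gives the only defined renal outcome: "AKI will be defined as stage 1, 2 or 3 according to VARC-2 AKI classification". Contrast induced nephropathy appears only in the statin objective and has no definition. Among the reasons for AKI after TAVI, the Discussion names "peri-procedural bleedings, hemodynamic instability, distal embolization and the use of nephrotoxic drugs".

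Statistical analysis first says that endpoints are compared in the two study arms, and then: "Between-group comparisons of clinical endpoints, biomarkers, and imaging data will be performed using the Mann-Whitney U, independent Student’s t tests, or chi square test". It names no regression or other adjusted method and gives no method for comparing statin users with non-users.

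**The concern.** Asking whether a drug brings benefit in preventing an outcome is asking for a treatment effect. The neighbouring objectives use the language of prediction, so non-causal wording was available and was not used here.

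Chronic use is by its nature a prior prescribing decision. Users and non-users may differ in vascular disease and in other factors that affect renal risk. Randomising the RenalGuard mode balances the two arms; it does nothing to balance statin users against non-users.

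The outcome term is a second, smaller problem. The same sentence uses AKI for two objectives and contrast induced nephropathy for this one, so it is unclear whether a different outcome is meant. If VARC-2 AKI is meant, the label claims a contrast mechanism that the outcome does not isolate.

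At stake is what may be concluded. Read literally, the objective invites a statement that statins do, or do not, prevent contrast nephropathy, and the design supports neither.

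**Working it through.** **1. The plan's own figure.** The only sample-size figure concerns the RenalGuard comparison (Power analysis: 40% against 20% AKI, two-sided 5%, 80% power, 92 per group).
- Pooled two-proportion formula: n = [1.96·√(2·0.30·0.70) + 0.842·√(0.40·0.60 + 0.20·0.80)]² / 0.20² = 81.2, so 82.
- With continuity correction: n' = (n/4)·[1 + √(1 + 4/(n·0.20))]² = 90.9, so 91.

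The stated 92 is thus reproduced to within one patient, with the correction. Nothing below changes it. The article gives no figure for the statin objective.

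**2. Objective against design.**

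| Element | Objective | What the article provides |
|---|---|---|
| Exposure | chronic statin treatment | prior use, not randomised |
| Outcome | contrast induced nephropathy, undefined | VARC-2 AKI stage 1 to 3, with non-contrast causes acknowledged |
| Claim | benefit in preventing | at most an association |
| Analysis | none stated | unadjusted tests, described for the two arms |

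**3. How far confounding could move a crude comparison (illustration).** The article gives no confounder prevalence or risk ratio, so all inputs here are assumed. Take no true statin effect and one binary risk factor with risk ratio RR for AKI, present in a share a of users and b of non-users. The crude risk ratio is [1 + a(RR − 1)] / [1 + b(RR − 1)].

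| RR | a = 60%, b = 40% | a = 70%, b = 30% |
|---|---|---|
| 1.5 | 1.30/1.20 = 1.08 | 1.35/1.15 = 1.17 |
| 2 | 1.60/1.40 = 1.14 | 1.70/1.30 = 1.31 |
| 2.5 | 1.90/1.60 = 1.19 | 2.05/1.45 = 1.41 |
| 3 | 2.20/1.80 = 1.22 | 2.40/1.60 = 1.50 |

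If the risk factor were instead commoner in non-users, the ratios invert. For example, 1/1.19 = 0.84 would look like a statin benefit.

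**4. What a crude comparison could detect (illustration).** Evaluable patients: 220 × 0.95 = 209. Overall AKI: (40% + 20%)/2 = 30%, about 63 events. The share of statin users is not given, so a range is assumed. The detectable difference d at 80% power solves d = 1.96·SE₀ + 0.842·SE₁, with SE₀ pooled, SE₁ unpooled and the overall rate held at 30%.

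| Users | d | AKI, users vs non-users | Risk ratio |
|---|---|---|---|
| 50% | 17.7 points | 21.1% vs 38.9% | 0.54 |
| 70% | 19.6 points | 24.1% vs 43.8% | 0.55 |
| 80% | 22.6 points | 25.5% vs 48.1% | 0.53 |

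Fixing AKI at 30% in non-users instead, with 30%, 50% or 70% users, gives 17.6, 16.0 and 16.9 points. On either basis only about a halving of AKI, or more, would be reliably detected, so a non-significant result would not show absence of benefit.

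**The case against.** The strongest reply is that nothing in the article commits the trial to a defective analysis. Most of that stands.

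- **The tests.** A reader might infer that the statin comparison will be an unadjusted chi-square test and hence that a confounded result will be reported. The article does not say so. Statistical analysis speaks of the two study arms, where unadjusted tests are legitimate. Those tests could not serve the neighbouring prediction objectives either, so the section evidently does not cover this group. Adjustment may be specified in a full protocol or analysis plan that is not shown, and its absence from the article is not counted as a fault here.
- **The outcome.** A reader might infer that the trial does not measure the outcome at all. That goes too far. Creatinine is measured, VARC-2 AKI is defined, and it is the evident candidate. The gap is one of terms.
- **RenalGuard as a source of bias.** Half of the patients receive an intervention assumed to halve AKI, but because it is randomised it is independent of prior statin use in expectation and does not confound the comparison.
- **Prescribing by treating physicians.** The sentence "Specific agents added or withdrawn will be made by treating physicians and will not be influenced by the study team" might be read as explaining how statin use arose. It closes a paragraph on care after the procedure and says nothing about chronic use. The word chronic alone shows that the exposure is not allocated.
- **Size and power.** The magnitudes rest on assumed inputs, and low power is expected for an objective on which the sample size was not based.

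What does not fall is the wording itself. No analysis plan can turn prior use into an allocated treatment, and adjustment reaches only the confounders that are recorded.

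**Conclusion.** The point holds as a minor one. The article states a causal secondary objective that its design cannot answer causally, on an outcome term it does not define. An observational association between baseline statin use and VARC-2 AKI can be estimated, and that is the most the trial can offer here.

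How much confounding there would be is unknown. Under the assumptions shown, a crude risk ratio of 1.08 to 1.19 could arise with no statin effect, and up to 1.50 under strong imbalance. These figures show that the issue could be material; they do not measure an error in the document. The randomised comparison of active with passive RenalGuard, its alpha and its sample size are untouched.

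**What to change.** Restate the objective as exploratory: the association of chronic statin use at baseline with VARC-2 AKI, as defined for the primary endpoint. If a distinct contrast-related outcome is really intended, define it separately.

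Estimate the association with a parsimonious logistic model containing statin use, randomised arm, baseline eGFR and a few key recorded comorbidities. The arm is included because it is expected to be a strong predictor of AKI, not to remove bias. With about 63 expected events, six terms leave roughly ten events per term (63/6 = 10.5), so the list should be short and fixed before the data are analysed. Report the odds ratio with its confidence interval, and make no claim of prevention or of its absence.

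The cost is a change of wording and one regression. The baseline medical history and interview should supply the covariates, assuming that statin use and the chosen comorbidities are recorded there. With 41 of 220 patients recruited at the time of the article, the change could be made well before analysis. The downside is a weaker claim for this one objective.
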